## Abstract

**Background:**

Repetitive transcranial magnetic stimulation (rTMS) has been investigated as a new tool in neurological rehabilitation of individuals with spinal cord injury (SCI). However, due to the inconsistent results regarding the effects of rTMS in people with SCI, a randomized controlled double-blind crossover trial is needed to clarify the clinical utility and to assess the effect size of rTMS intervention in this population. Therefore, this paper describes a study protocol designed to investigate whether the use of rTMS can improve the motor and sensory function, as well as reduce spasticity in patients with incomplete SCI.

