Protocols involving rTMS have been used to induce changes in the excitability of neuronal circuits with positive effects [11–16] at the site of stimulation or transsynaptically at distant sites such as spinal cord circuits [17, 18]. The effect of high-frequency rTMS (i.e. ≥ 5Hz) includes changes in synaptic plasticity resembling long-term potentiation (LTP), as well as shifts in network excitability, activation of feedback loops, and activity-dependent metaplasticity [19, 20]. On this basis, rTMS is emerging as a promising technique in improving neurophysiological outcomes and voluntary motor output in patients with motor disorders [11, 21, 22]. Indeed, studies indicate that motor improvements may be due to modification of corticospinal projections by increasing motor cortical excitability [14–16] and, consequently, promote plasticity associated with functional recovery [22]. Additionally, reduction in spasticity may occur through enhancement of descending corticospinal projections and segmental effects on spinal interneurons that might strengthen inhibitory connections [13, 14, 23].

Many studies have used rTMS as a non-invasive and painless method to induce long-lasting changes in the excitability of cortical and corticospinal pathways after iSCI. In this scenario, rTMS has been found effective in enhancing corticospinal synaptic transmission [12], reducing spasticity [13, 14, 23] and improving sensorimotor function after iSCI [14–16], although we note none of these studies reported associated effect sizes in their analyses. However, other studies report less positive findings, including unchanged sensorimotor function [24], as well as unaltered cortical excitability and level of spasticity [16] in response to rTMS. The lack of consistent results is likely associated with differences in stimulation parameters (e.g. intensity, frequency, number of pulses), number of sessions, relative location of M1, chronicity and levels of injury, and outcome measurements used in previous studies [10].

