### Statistical analysis

#### Sample size

The sample size was calculated using statistical software (GPower 3.1.5) [57] on the main outcome measure (i.e. the motor score). This calculation was based on data from one study with a group of SCI individuals that received high-frequency rTMS at a frequency of 5 Hz on the vertex, which related to an improvement in clinical measures of the motor score [24]. The power was 0.80; the alpha was 0.05, the effect size was 0.65 (Cohen’s *d*). The sample estimation indicated that 14 participants would be necessary (i.e. seven per group). With an adjustment to allow for a dropout rate, we will recruit 20 participants.

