#### Data analysis

The analysis will follow a pre-specified analysis plan, based on comparing the groups as randomized (intention-to-treat). All data will be presented as mean ± standard deviation and summarized in frequency tables. We will use Microsoft Office Excel for Windows (version 2013) to store the data and the Statistical Package for Social Sciences (SPSS-IBM®) version 21 for Windows to perform statistical analysis. The normality and homogeneity of all variables (i.e. primary and secondary outcomes) will be tested with the Shapiro–Wilk and Levene’s test, respectively. For non-parametric data, the Friedman test will be used followed by the Wilcoxon post hoc test. We will use the ANOVA two-way (2 × 4) for the inferential statistic of the parametric data, with Tukey’s post hoc tests. Significance level will be set as α ≤ 0.05 and the effect size will be calculated by eta-squared (*ŋ*
^*2*^).

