## Discussion

Individuals with iSCI show clinical symptoms which are associated with reduced quality of life and functional independence [60, 61]. The CNS may be able to recover naturally after injury due to plasticity mechanisms and reorganization of residual neural pathways [5]. However, natural recovery is limited and cannot be relied upon [6]. It is therefore plausible that stimulation as a rehabilitation technique may be crucial in enhancing CNS plasticity. High-frequency rTMS has emerged as a promising technique in stimulating neural reorganization and synaptic plasticity in cortical and subcortical networks, thereby affecting the descending control of spinal excitability [11, 12, 14, 34, 62, 63]. These mechanisms might accelerate the development of neural connectivity responsible for motor function improvement [12, 14, 22, 24, 63].

Although an adaptive reorganization involves the formation of new connections and restoration of pre-existing connections, studies that directly address quantitative parameters associated with neuronal repair are limited. This is because most of the outcome measures are not able to assess the neurophysiological substrates that directly contribute to functional recovery, such as specific mechanisms within the brain and spinal cord that influence the generation of the motor command to the affected limbs [63].

The protocol described herein is expected to be the first fully randomized controlled double-blind crossover trial to assess the effect sizes associated with rTMS intervention in participants with iSCI. We expect the outcomes of the present study to provide additional clinical evidence of the potential benefits of high-frequency rTMS applied to the lower-limb motor area to improve sensorimotor recovery and/or to reduce spasticity in patients with iSCI.

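### Assessing the effect size of rTMS is a stated purpose, but the only effect measure fixed for the results is eta-squared, which does not give the active-minus-sham effect or its precision

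*Protocol article*

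**What the plan says.** The Abstract (Background) gives two reasons for the trial: "to clarify the clinical utility and to assess the effect size of rTMS intervention in this population". The main Background section remarks of the earlier positive studies that "none of these studies reported associated effect sizes in their analyses". The Discussion presents the trial as the first of its kind "to assess the effect sizes associated with rTMS intervention in participants with iSCI".

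Under Sample size, planning used Cohen's d: "the effect size was 0.65". The article does not say whether this d is paired or between groups.

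Under Data analysis, the parametric route is: "We will use the ANOVA two-way (2 × 4) for the inferential statistic of the parametric data, with Tukey’s post hoc tests". The alternative is: "For non-parametric data, the Friedman test will be used followed by the Wilcoxon post hoc test". For the size of the effect the article says that "the effect size will be calculated by eta-squared". The same section promises means with standard deviations for all data. It names no other effect measure.

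Study design and Fig. 1 describe two sequence groups, each receiving active and sham stimulation in opposite order, assessed before and after each of the two periods. That makes four assessments.

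**The concern.** A trial that sets out to say how large the rTMS effect is needs an estimate of active minus sham, with a sign and a measure of precision. Eta-squared is a share of variance. It cannot be negative, its expected value is above zero when nothing is happening, and when it belongs to a multi-df ANOVA term it is not tied to one comparison. It is also on a different scale from the d used for planning.

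At stake is whether the headline effect size can be read as the effect of rTMS, compared with the planning assumption, or used by later trials. The three hypotheses in Background are directional (better motor function, better sensory function, less spasticity), so the sign matters.

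**Working it through.** **The plan's own figure.** Sample size gives 14 participants for d = 0.65, power 0.80 and alpha 0.05. Simple t-tests do not return 14. A paired test needs 21 (two-sided) or 17 (one-sided), and an independent two-sided test needs 38 to 39 per arm. Repeated-measures ANOVA settings come close or match if a correlation of 0.5 is assumed. The group-by-time interaction with f = 0.65/2 = 0.325 has power 0.788 at N = 14. Entering 0.65 as f in the between-groups test gives 0.806. A paired test also gives 14 if a correlation of 0.7 is assumed. The document therefore does not show what scale the planning d is on. That matters below only for comparing results with it.

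**Layout.** A condition by before/after layout would be 2 × 2. Two sequence groups and four assessments give 2 × 4, so the working takes sequence group × assessment. This is an inference.

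**Where the treatment effect sits.** Order the assessments as pre1, post1, pre2, post2. In the active-first group, active minus sham change is (post1 − pre1) − (post2 − pre2), with weights (−1, +1, +1, −1). In the sham-first group the signs reverse. The average over both groups is half the between-group difference in this contrast. That is one of the three degrees of freedom of the interaction.

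Suppose the true effect is δ and there are 10 per group.
- No carry-over: group means are (0, δ, 0, 0) and (0, 0, 0, δ). The interaction sum of squares due to treatment is 20 × 2δ²/4 = 10δ², and a further 20 × δ²/4 = 5δ² falls in the time term.
- Full, constant carry-over: group means are (0, δ, δ, δ) and (0, 0, 0, δ). The interaction now holds 20 × δ²/4 = 5δ², and the time term 20 × δ²/2 = 10δ².
- The weighted contrast equals δ in both cases.

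Simulated averages (N = 20, δ = 0.65 SD, assumed correlation 0.5) agree:

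| Setting | Partial eta², interaction | Partial eta², time |
|---|---|---|
| Effect +0.65 SD | 0.172 | about 0.12 |
| Effect −0.65 SD | 0.172 | about 0.12 |
| Effect +0.65 SD, full carry-over | 0.116 | 0.170 |
| No effect, common trend 0, 0.3, 0.3, 0.6 SD | 0.053 | 0.155 |

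The first two rows show the lack of sign. The third shows the interaction measure falling by a third although the difference in change is the same. The fourth shows the time term picking up a trend that has nothing to do with treatment, while the interaction stays at its null value.

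**Bias with no effect.** For the interaction, df1 = (2 − 1)(4 − 1) = 3 and df2 = 3(N − 2). The expected partial eta-squared is df1/(df1 + df2).
- N = 20: 3/(3 + 54) = 0.053, with 95th percentile 0.134. The value is 0.06 or more in 34% of trials.
- N = 14: 3/(3 + 36) = 0.077, with 95th percentile 0.193.

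The article says eta-squared, not partial eta-squared. Classical interaction eta-squared with no effect at N = 20 averages 0.020 at correlation 0.5 and 0.008 at correlation 0.8 (simulated).

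**Bias with an effect.** For a paired contrast the population value is d²/(1 + d²). At N = 20:
- d = 0.30: 0.09/1.09 = 0.083, estimated on average as 0.122.
- d = 0.65: 0.4225/1.4225 = 0.297, estimated on average as 0.318, a ratio of 0.318/0.297 = 1.07.

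**What a signed estimate would give.** The 95% half-width of the crossover contrast is t(0.975, N − 2)/√N, in SDs of the within-person difference. This is 0.47 at N = 20 and 0.58 at N = 14. As an illustration, an observed paired standardised difference of 0.65 has a 95% CI of 0.16 to 1.13 at N = 20 and 0.06 to 1.22 at N = 14 (noncentral t).

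**The case against.** Several stronger readings are tempting, and the document does not support them.

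- A reader might infer that improvement could not be told from worsening. That is not so. Means with standard deviations are promised and post hoc comparisons are planned, so direction will be visible. What those tables lack is the within-person difference and its precision, because the SD at each visit does not give the SD of the difference.
- A reader might infer that the interaction mixes treatment with period effects. A period effect common to both sequences goes into the time term. Only carry-over disturbs the interaction.
- A reader might take 0.053 to 0.193 as the size of the problem. Those figures are for partial eta-squared. The classical version is inflated far less, and a significance test would accompany either.
- A reader might say that the trial exists solely to estimate an effect size. Clinical utility is named beside it.
- A reader might set a paired standardised difference directly against 0.65. The article never says that the planning d is paired.

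It can also be said that intervals and exact contrasts belong to the analysis plan that Data analysis refers to. That is fair, and the absence of an interval from a condensed article is not the point here. The article does make a choice, however: it fixes eta-squared as the effect size. A separate plan might add a signed contrast, but the published text commits to a measure that does not answer the stated question.

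**Conclusion.** The concern stands in limited form. Eta-squared alone does not deliver the effect size that the trial says it will assess. It is unsigned and, on the natural reading of 2 × 4, no ANOVA term equals active minus sham. It is also biased upward at this sample size.

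The bias is the weaker part. With no effect the average is 0.053 to 0.077 as partial eta-squared for N = 20 down to 14, but about 0.008 to 0.020 as classical eta-squared at N = 20. It is noticeable for small effects (0.122 against 0.083 at d = 0.30) and about 7% at d = 0.65 for a paired contrast. The stronger part is that neither eta-squared nor the visit-wise SDs give the within-person treatment effect and its precision.

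The assumptions are the sequence-by-assessment layout and within-person correlations of 0.5 to 0.8, neither of which the article states. The lack of sign and the upward bias do not depend on the layout. Nothing here affects the conduct of the trial, and it should be corrected before analysis.

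**What to change.** 1. Make the main effect estimate the mean active-minus-sham difference in pre-to-post change in ASIA motor score, in points, with a 95% CI, from a crossover contrast that accounts for period.
2. Add a small-sample-corrected standardised difference with its CI, and state the standardiser. Compare it with the planned d = 0.65 only if the two are on the same scale.
3. Do the same for the secondary scores, with a rank-based estimate and CI for the ordinal Modified Ashworth grades.
4. Name the two factors of the ANOVA if it is kept. Report eta-squared as a supplement at most, stating whether it is classical or partial and to which term it belongs.

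This uses only data already planned for collection. The cost is revised wording and a little more analysis work.

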### Expected risks

High-frequency rTMS is a safe non-invasive technique according to current knowledge [9, 58]. Some studies indicate that there may be weak tension headaches and muscle spasms experienced during rTMS [59]. Overall, in cases where contraindications or safety parameters were not maintained, serious adverse events such as seizures occurred [9]. According to Rossi et al. [9], a large number of individuals were subjected to studies with rTMS since 1998 (when the limit parameters by Wassermann et al. [58] were defined) and a small number of seizures were observed. Therefore, the risk of rTMS-induced seizures is considered very low. To avoid adverse effects and risks to the individual, the rTMS parameters used in the present trial will be within the safety limits set by the NINDS and by Rossi et al. [9], which were updated security settings for transcranial magnetic stimulation.

### Expected benefits

Intervention with high-frequency rTMS over the parameters established in this study may generate motor gains and consequent functional recovery in patients with iSCI. Motor gains and functional recovery might contribute to an improved quality of life and functional independence. Moreover, the participation of those in this study will contribute towards the construction of scientific knowledge on the use of rTMS in iSCI.

## Discussion

Individuals with iSCI show clinical symptoms which are associated with reduced quality of life and functional independence [60, 61]. The CNS may be able to recover naturally after injury due to plasticity mechanisms and reorganization of residual neural pathways [5]. However, natural recovery is limited and cannot be relied upon [6]. It is therefore plausible that stimulation as a rehabilitation technique may be crucial in enhancing CNS plasticity. High-frequency rTMS has emerged as a promising technique in stimulating neural reorganization and synaptic plasticity in cortical and subcortical networks, thereby affecting the descending control of spinal excitability [11, 12, 14, 34, 62, 63]. These mechanisms might accelerate the development of neural connectivity responsible for motor function improvement [12, 14, 22, 24, 63].

Although an adaptive reorganization involves the formation of new connections and restoration of pre-existing connections, studies that directly address quantitative parameters associated with neuronal repair are limited. This is because most of the outcome measures are not able to assess the neurophysiological substrates that directly contribute to functional recovery, such as specific mechanisms within the brain and spinal cord that influence the generation of the motor command to the affected limbs [63].

The protocol described herein is expected to be the first fully randomized controlled double-blind crossover trial to assess the effect sizes associated with rTMS intervention in participants with iSCI. We expect the outcomes of the present study to provide additional clinical evidence of the potential benefits of high-frequency rTMS applied to the lower-limb motor area to improve sensorimotor recovery and/or to reduce spasticity in patients with iSCI.

### Trial status

Participant recruitment started in May 2017 and is expected to end in November 2017. Study completion is estimated by May 2018.

## Abbreviations

ASIA: American Spinal Injury Association Impairment Scale
CAEE: Certificado de Apresentação para Apreciação Ética (in Portuguese)
CAPES: Coordination for Higher Education Staff Development (in Portuguese)
CNS: Central nervous system
CST: Corticospinal tract
EEG: Electroencephalogram
EMG: Electromyography
FAPESP: Foundation of Support for Research of São Paulo State (in Portuguese)
FMS: Fugl–Meyer Scale
HAM-D: Hamilton Rating Scale for Depression
iSCI: Incomplete spinal cord injury
ISNCSI: International Standards for Neurological Classification of Spinal Cord Injury
LE: Lower extremity
M1: Primary motor cortex
MAS: Modified Ashworth Scale
MMSE: Mini-Mental State Examination
NE: Neurological examination
NINDS: National Institute of Neurological Disorders and Stroke
rTMS: Repetitive transcranial magnetic stimulation
SCI: Spinal cord injury
SDQ: Socio-demographic questionnaire
SENIAM: Surface Electromyography for the Non-Invasive Assessment of Muscles
SPIRIT: Standard Protocol Items: Recommendations for Interventional Trials
SPSS: Statistical Package for Social Sciences
UE: Upper extremity
